### Limitations

There are limitations of this study. Each of these limitations is briefly considered below.
**Study design:** The retrospective nature of aim 1 and aim 3 in the study for LPG adopters might lead to concerns of recall bias, which may limit the accuracy of participants’ memories on factors of 3As, which impacts adoption. However, engaging a large sample size of 510 households in such geographically proximal households might reduce the issues of recall bias [43]. Similarly, the retrospective nature of data from follow-up questionnaire for aim 2 might also be subject to recall bias.
**Data analyses:** Regression of sustained use (SUMS data) on its determinants (3As) (from follow up questionnaires) will be done for a small sample size of 100 households. Smaller sample size might preclude us from conducting multilevel analyses by controlling for institutional level predictors.
**Exploratory study:** There is limited empirical evidence available on the impact of 3As on adoption and sustained use of LPG. This study is primarily exploratory and developmental in nature. However, it is expected that this study will inform future research to develop and test the effectiveness of implementation strategies for LPG adoption and use in resource poor settings within the RE-AIM framework. In addition, findings from the study will provide insights on the estimate of effect size to facilitate a larger R01 study on the impact of 3As on LPG adoption and sustained use in such communities.

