### Sampling and recruitment

We will undertake a case control study in the rural habitations of Thambalpalle and Peddamandyam mandals (block) in Chittoor district of Andhra Pradesh state in India [27]. Our implementing partner, Foundation for Ecological Security (FES) has extensive field experience working in this region and we will leverage their expertise and understanding of social, economic, and demographic characteristics of the households in these habitations.

We will select an equal number of case and control households for this proposed study (control to case ratio will be 1:1). We will select a sample size of 255 households each for case (LPG adopter households) and control (LPG non-adopter households). A total sample size of 510 households at a 95% confidence level (alpha = .05) will provide a power of 80% to this study at a control to case ratio of 1. This computation assumed that the populations mean difference in monthly income was 545.35 India National Rupee (INR), and the common within-group standard deviation was 2199.26 INR per month. In the absence of previously published studies on rural income in this region, where the study is to be undertaken, the power computation was conducted using a baseline income data from another recently concluded NIH funded R21 (WUSTL IRB ID# 201207016) randomized controlled trial (RCT) on cookstoves. This study will be conducted in the same region where the RCT was undertaken. To calculate the sample size, we used the Power and Precision 4 software. The criterion for significance (alpha) was set at 0.05. The test was 2-tailed, and so an effect in either direction will be interpreted. With the proposed sample size of 255 each for case and control group, the study will have power of 80% to yield a statistically significant result. It is also assumed that this effect size is reasonable; an effect of this magnitude could be anticipated in this field of research. On average, a study of this design would enable us to report the mean income difference with a precision of 95% confidence level.

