We use a multistage random sampling to select households in these rural habitations. To facilitate sample selection, we develop an exhaustive list of habitations (and households in these habitations) with four key variables: 1) distance to nearest LPG distribution center; 2) dominant caste of the habitation; 3) number of households in each habitation; 4) presence of LPG adopters in these habitations. A multistage sample selection process will be conducted using the following steps in their respective order:
**Sample of habitations:** We will use stratified random sampling to select the list of villages for the study. The selection criteria are:

*Proximity to the nearest LPG distribution center:* Based on the distance from the nearest LPG refilling and distribution center, we divide the exhaustive list of habitations (i.e. habitations population list) in two sub-groups: near to the center and far from the center, by taking a median split of the distance of the habitation from the LPG distribution center.
*Dominant caste of the habitation:* We divide the habitations population list into three sub-groups: General Caste, Other Backward Castes (OBC), and Scheduled Castes/Scheduled Tribes (SC/ST).

These two stratifying variables and their subgroups will lead to six distinct strata (2subgroups*3subgroups). We will divide the habitations population list across these six distinct strata. We will select a total sample of 35 habitations from these six distinct strata. Table 1 shows an indicative list of the six distinct strata that will be used to select the final 35 habitations.2.We have data on the number of LPG adopters and non-adopters from each of these selected habitations. We will use quota sampling to select households from each of these habitations. We will randomly select 255 LPG adopter households (case) from these 35 habitations. Subsequently, we will select as many non LPG adopter households (control) as we have LPG adopters (case) across each of the habitations. This will ensure a case control design in every habitation, with a control to case ratio as 1, and a total sample size of 510 households.

**Table 1 Tab1:** Exhibit list of stratified random sample of habitations

Strata	Proximity to LPG distribution centers	Dominant caste
1	Near	General
2	Near	OBC
3	Near	SC/ST
4	Far	General
5	Far	OBC
6	Far	SC/ST

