### Data collection

#### Aim 1: To understand how rural LPG adopters vary from other rural households on factors of affordability, accessibility, and awareness of LPG

A structured household adoption questionnaire will be used to record data on social, economic, and demographic characteristics. Women (primary cook) from each household will be the respondent for this questionnaire. In addition to household demographic characteristics, the questionnaire will record data pertaining to the 3 significant drivers impacting LPG adoption: affordability, accessibility, and awareness (3As) of LPG. The categorical outcome variable for aim 1 will be adoption of LPG at the time when data collection is undertaken for the household. Candidate variables on affordability include household income, upfront costs to acquire LPG, access to bank loans, facility of payment in installments for LPG purchase and refill, regularity of income (in past 12 months), and women’s financial autonomy. Candidate variables on accessibility include distance of habitations and households from LPG distribution centers, presence of paved roads to LPG distribution centers, and nature of LPG cylinders’ home delivery system. Candidate variables for awareness include government promotion campaigns, local self-government *(Gram Sabha)* awareness drives, and participation of women in self-help groups. In addition, we will capture data on how organizations at the community level, including government entities, and LPG distributors shape household adoption and sustained use of LPG. Candidate organizational factors are irregular supply and bureaucratic hurdles to apply for LPG, which will be assessed from the perspective of households. Key control variables that will be recorded are caste, household size, months of LPG ownership (in case group), educational status of household head, and free availability of biomass. This adoption questionnaire for aim 1 will be administered to all 510 households immediately after their enrollment in the study.

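### The Limitations section credits sample size and proximity with reducing recall bias, which neither can do; state it as a residual limitation and quantify it for the recalled aim 1 items

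*Protocol article*

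**What the plan says.** Under Limitations (study design), the article concedes that "The retrospective nature of aim 1 and aim 3 in the study for LPG adopters might lead to concerns of recall bias". The next sentence gives the only countermeasure it presents as such: "engaging a large sample size of 510 households in such geographically proximal households might reduce the issues of recall bias".

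Other sections bear on the point:

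- **Who answers.** In the aim 1 data collection section, the woman who is the primary cook answers one structured questionnaire, the same in both groups, on affordability, accessibility and awareness. Items include upfront costs, the delivery system and promotion campaigns. Others lean less on memory, such as "distance of habitations and households from LPG distribution centers, presence of paved roads to LPG distribution centers". The sampling section already lists "distance to nearest LPG distribution center" for every habitation.
- **Eligibility.** Under Study participants, case households must have received their first cylinder within the 12 months before enrollment. No matching reference date is given for controls.
- **Selection.** Under Sampling and recruitment, each habitation contributes as many controls as cases, 255 of each overall.
- **Aim 3.** The data collection section and Table 2 give 100 case and 100 control households, not 510.

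**The concern.** Recall error in a case-control comparison has two parts. Random error averages out as households are added. A systematic difference between groups does not. Adopters have recently been through acquiring LPG and may remember campaigns, costs and delivery arrangements more fully than non-adopters. If so, every added household carries the same expected error, and the estimate settles more firmly on the wrong value.

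Proximity may balance what adopters and non-adopters were exposed to in their area. It does not balance how well they remember it.

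The stake is how the aim 1 odds ratios are read. The Limitations section expects the study to supply effect-size estimates for a larger study, and the Discussion ties the lessons to LPG policy. An odds ratio shifted by recall would carry into both, and a larger follow-on study using the same questions would reproduce it with a narrower interval.

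**Working it through.** **1. The plan's own sample size.** Inputs from Sampling and recruitment: income difference 545.35 INR, SD 2199.26 INR, two-sided alpha 0.05, power 80%.

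n per group = 2 × (1.960 + 0.842)² × (2199.26 / 545.35)² ≈ 255.3, rounded up to 256. At 255 per group, z = 545.35 / (2199.26 × √(2/255)) = 2.80, and power = Φ(2.80 − 1.96) = 79.95%. The stated 255 and 80% reproduce. The formula contains only random error; it has no term for bias.

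**2. Differential recall with no true association.** All recall figures here are assumptions. Let π be true exposure (equal in both groups), Se the share of exposed households reporting it, and Sp the share of unexposed households correctly reporting none.

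- Reported exposure: p = π × Se + (1 − π) × (1 − Sp)
- Odds ratio: [p₁/(1 − p₁)] / [p₀/(1 − p₀)], which does not contain n
- Standard error of the difference: √{[p₁(1 − p₁) + p₀(1 − p₀)] / n}
- Chance of p < 0.05: Φ(|p₁ − p₀|/SE − 1.96) + Φ(−|p₁ − p₀|/SE − 1.96)

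Worked case, π = 0.50, Sp = 1, recall 90% versus 70%: p₁ = 0.45, p₀ = 0.35. OR = (0.45/0.55)/(0.35/0.65) = 1.52. At n = 255, SE = √[(0.2475 + 0.2275)/255] = 0.0432, z = 0.10/0.0432 = 2.32, and the chance is Φ(0.36) ≈ 64%.

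| π | Sp | Recall, cases vs controls | Reported exposure | OR at any n | False significance, n = 100 per group | n = 255 | n = 1,000 |
|---|---|---|---|---|---|---|---|
| 50% | 100% | 90% vs 90% | 0.45 vs 0.45 | 1.00 | 5% | 5% | 5% |
| 50% | 100% | 90% vs 80% | 0.45 vs 0.40 | 1.23 | 11% | 21% | 62% |
| 50% | 100% | 90% vs 70% | 0.45 vs 0.35 | 1.52 | 31% | 64% | over 99% |
| 30% | 95% | 90% vs 80% | 0.305 vs 0.275 | 1.16 | 8% | 12% | 32% |
| 30% | 95% | 90% vs 70% | 0.305 vs 0.245 | 1.35 | 16% | 33% | 85% |

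Within each row the odds ratio is fixed. Where recall differs, only the chance of false significance moves, and it rises with n. These are crude comparisons that ignore clustering by habitation.

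**3. The same on the plan's income scale.** Assume a 200 INR reporting difference and no true difference. The bias stays at 200 INR, while the 95% half-width, 1.96 × 2199.26 × √(2/n), falls from 610 INR (n = 100) to 382 (n = 255) to 121 (n = 2,550). The chance of a significant result rises from 10% to 18% to 90%.

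**4. Scope.** For aim 3 the relevant sample is 100 + 100 = 200 households, so a claim resting on 510 could not cover it.

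**The case against.** The case for the protocol has several strands.

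- **Tone and weight.** The sentence is hedged, sits among openly declared limitations in a study called exploratory, and cites a source not available here. No sample size or analysis rests on it. This stands and keeps the point modest. A reader might infer that the authors will present their odds ratios as protected by the sample size; nothing in the article says so.
- **Existing restraint.** A reader might infer that recall bias is left wholly unaddressed. That is too strong. The first-cylinder rule bounds the cases' window, both groups get the same structured questionnaire from the same type of respondent, and distance is already on the sampling list. These features limit recall error, though none is offered as a control for it and none removes a difference between groups.
- **Unknown size.** The article speaks of less accurate memories and gives no recall rates. That recall differs between adopters and non-adopters is plausible but assumed. If error were equal in both groups, a binary association would mainly be diluted, which a larger sample does not cure either.
- **Record-based substitutes.** A reader might infer that road access, delivery or campaigns should be recorded once per habitation instead of asked of households. The sampling rules this out. With equal cases and controls in each habitation, a variable with one value per habitation has the same distribution in both groups, so its crude odds ratio is 1 whatever the truth. A field log of campaigns would also not measure awareness, which the article defines by what households know and perceive.

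**Conclusion.** The sentence credits the design with a property it lacks. A larger sample does not reduce a case-control recall difference, proximity does not equalise recall, and the figure of 510 does not describe aim 3. Recall bias therefore remains a residual limitation of aims 1 and 3.

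The size cannot be fixed from the article. Under the assumed 10- and 20-point recall gaps, a true odds ratio of 1 appears as 1.16 to 1.52, with a 12% to 64% chance of false significance at 255 per group against a nominal 5%. These are illustrations, not estimates. They depend on true exposure, on false reporting by unexposed households, and on recall actually differing. A reader might take 64% as this study's false-positive rate; the documents do not support that. Nor do they show that any particular odds ratio will be biased, or that the number of households should change.

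**What to change.** 1. Delete the claim that sample size or proximity reduces recall bias. State recall bias as a residual limitation of aims 1 and 3. The first-cylinder rule may be mentioned as bounding the cases' recall window, not as a control for differential recall.
2. Mark the aim 1 items that rest on memory, such as campaign exposure, costs and delivery, as recall-dependent.
3. For each marked item, report how far an assumed case-control recall difference (for example 90% versus 80%, and 90% versus 70%) would move its odds ratio, with the assumed exposure and specificity stated.
4. Keep the household reports. Do not replace them with one value per habitation.

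The cost is a few sentences and a short sensitivity calculation on data already planned. The limitation will read less favourably than it does now.

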## Discussion

In this study we bring three novel approaches together to gain new insights:Apply the RE-AIM (Reach, Effectiveness, Adoption, Implementation, and Maintenance) framework to explore LPG adoption and use. RE-AIM framework will guide this research and development of measures for reach, adoption, implementation, and maintenance in the clean cooking sector.Delineate adoption and sustained use as separate outcomes and analyze them as a function of affordability, accessibility, and awareness (3As) of LPG.Deploy Social Network Analysis (SNA) to understand how gender networks matter in dissemination of awareness and consequently in adoption of LPG.

In combining these approaches, we will be able to: 1) examine the pooled impact of the 3As on LPG adoption and sustained use, absent in the present stock of research; 2) assess the relative influence of personal gender networks of men and women on the adoption and sustained use of LPG, contributing to our understanding of the role of gender networks in the implementation of clean cooking, 3) understand these effects through the RE-AIM framework to apply our insights toward implementation of cleaner fuels and advance implementation science in the clean cooking sector. This will be the first systematic study to use personal social networks striated by gender to analyze LPG adoption in rural India. Lessons drawn from this study are timely, relevant, and of interest to Government of India’s renewed focus on policy design (including provisions in annual budget 2016) and implementation to expand LPG distribution to the poor in rural India [8, 9, 44]. The Government of India (GOI) has committed to redesigning their LPG policy and distribution to penetrate rural communities using a combination of direct cash transfer programs (PAHAL), campaigns encouraging non-poor to give up LPG subsidies (GiveItUp campaign), and smaller LPG cylinders [9]. Systematic research is needed to undertake a concurrent analysis of the 3As and their corresponding impact on both adoption and sustained use of LPG in rural hosueholds. Careful assessment of the elements of 3As could facilitate a model of a succesful pro-poor strategy for LPG uptake and sustained use.
